**Figure 2 figure2:**
[figure not shown]
Diary view format introduced after modifications to enhance usability of OHP.

Upon enrollment, patient participants undergo individual semistructured 30 to 45 minutes induction by the lead researcher or research assistants.

The induction is hands-on and covers the initial set-up with participants practicing all the tasks they are expected to perform independently from then on. Induction covers signing up, logging on, navigating through the OHP Web portal, data entry, messaging, and reviewing data trend/summary graphs. All data entry is practiced using the previous day’s data. Performing BGL self-monitoring, administering insulin, and following dietary advice are part of routine diabetes education and counseling provided by a multidisciplinary endocrinology care team as described under usual care. Participants are also instructed on how to share this health information with the GDM clinicians for the purpose of providing clinical care and with the project lead investigator for research data collection and data management purposes. When required and in order to improve study data collection, the lead researcher may set up automatic reminders on OHP to send reminders every second day to prompt the noncomplying patient to enter data. Activating or setting up automated reminders is not routine but it is targeted for those who fail to perform data entry according to expectations. This avoids inundating those who are compliant with unnecessary reminders.

Participants are asked to enter their GDM self-monitoring data onto OHP daily or every other day in order to minimize backlogs and associated data entry errors. Maintaining a paper diary is optional. Automated alerts about new data entries are sent to the clinicians via email prompting the clinicians to log in under their credentials to review the patient data. When required and depending on the reviewed data or patient queries, clinicians provide feedback to the patient via the messaging service about any necessary alterations to treatment (eg, insulin titrations, changes to diet). The CDE-RNs act as the gatekeepers to interact with the telemedicine system and to consult or liaise with other GDM service team members. Patients can also email or print reports for other interested parties who do not have direct access to the Web-based shared data.

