Induction for clinicians involved in providing care was conducted by the lead researcher. It consisted of setting up log-on credentials, using and navigating through the OHP webpage, setting up alerts, reviewing patient data, and messaging. The induction included both demonstration and hands-on practice in group setting.

Tasks expected of clinicians are to review patient data at their convenience, fitting in with their other routine clinical commitments through the day during weekdays. At the minimum, data are reviewed every 1 to 2 days during the week. Clinical decision making and advice in relation to ongoing management of GDM is at the discretion of the clinicians in accordance with existing clinical protocols without interference from the researchers. The same applies to scheduling of clinic appointments. Clinicians may also remind a patient when no data have been entered.

For research data collection, participant engagement, and/or troubleshooting purposes, the lead researcher periodically contacts participants via the OHP messaging feature or telephone and extracts all data from OHP to collate in a secure MS Access study database. The lead researcher is the primary contact for basic technical support queries, escalating any queries that cannot be resolved to the OHP vendor.

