The primary outcome of the quantitative exploratory RCT component of the study is service utilization. Maternal and fetal outcomes, satisfaction, and costs are secondary outcomes. In particular, one of the limitations of studies in our systematic review [11] was the lack of cost evaluation, however basic. Considering that studies appear to show virtually similar clinical outcomes between telemedicine and usual care/control [12,17-19], a form of cost comparison becomes important. There are several methods for undertaking health economic evaluation, one of which is cost minimization. This type of health economic evaluation is defined as “. . . evaluation method to use when the case for an intervention has been established and the programmes or procedures under consideration are expected to have the same, or similar, outcomes. In these circumstances, attention may focus on the cost side of the equation to identify the least costly option” [39]. At the time of this protocol study, patients not covered by the Australian Medicare paid AUD $280 for each face-to-face consultation with a clinician for GDM care at the centers in this study. Because diabetes education, endocrinology, and dietetics are the key outpatient specialties involved directly in GDM management and therefore targeted for influence by the TeleGDM intervention, the AUD $280 cost rate will be assigned to these for service provided to patients between study entry and study exit. Study participant outpatient consultations data covering service access between commencement of recruitment and end of data collection for computation of provider costs will be sourced from the hospital data management unit. While clinicians provide service over the phone, which is a cost to the hospital, patients are not billed and hence this cost will not be included. Furthermore, implementing the intervention required existing equipment and infrastructure for the brief induction. Costs for these were considered negligible and therefore were not taken into consideration. Also Australian public hospitals by their nature are nonprofitmaking entities. Where fees are charged these are normally break-even and include overheads. Besides the AUD $85 per patient subscription there is no separate license fee for OHP.

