**Primary**					
	Patient service utilization	Patient control	Number of scheduled face-to-face consultations	Attendances and nonattendances from outpatient activity dataset; patient medical records	Study exit
			Number of unscheduled face-to-face consultations		
			Number of telephone consultations		

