**Tertiary**					
	Usage (patients and clinicians)	Technology capability	Clinician system, information and service quality, usage	Modified Canada Health Infoway System And Use Assessment Survey	6 months from beginning of study
			OHP access; volume of data uploaded	Extraction from OHP logs	Study completion

^a^BGL: blood glucose level

^b^OHP: Online Health Portfolio

^c^DES-SF: Diabetes Empowerment Scale–Short Form

^d^LGA: large for gestational age

^e^SCN: special care nursery

^f^NVD: normal vaginal delivery

^g^LUSC: lower uterine segment cesarean section

^h^CSQ-8: Client Satisfaction Questionnaire–8 Item (CSQ-8)

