### Strengths and Limitations

The strength of the TeleGDM is the innovative use of current technologies in GDM, particularly in the Australian context. Second, the study uses a mixed-method approach to enhance the rigor of the evaluation and incorporates elements of a framework proposed for evaluating telehealth interventions in Australia [41]. The study includes cost evaluation, an important consideration which telehealth studies are often criticized for excluding [10]. Costs are only considered from a provider perspective and limited to billable consultations for pragmatic reasons, a potential methodological limitation. As such, a full economic evaluation that takes into account other costs could be a future consideration.

Internet security is one of the barriers to uptake of Web-based interventions [46]. Hence OHP uses 256-bit data encryption, individual username and password access, and an inactivity timeout. Despite these security measures, data breaches cannot be completely ruled out. Any interactions over the Web carry the risk that user privacy and confidentiality may be breached, however minimal. This may happen as a result of unauthorized access during the course of transmission, hacking into system servers, or users not exercising due diligence in securing their log-on information.

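### Clinician work on the OHP portal enters neither utilization nor cost, which favours telemedicine; telephone care is left out of cost for a reason that does not fit a provider perspective

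*Protocol article*

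**What the plan says.** Table 1 gives the primary outcome, patient service utilization, three indicators: scheduled face-to-face consultations, unscheduled face-to-face consultations, and "Number of telephone consultations". OHP messages and clinician reviews of OHP data are not among them. OHP activity appears only as a tertiary technology outcome, where access and upload volume come from "Extraction from OHP logs".

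On cost, Data and Outcomes takes the outpatient specialties involved in GDM care (diabetes education, endocrinology, dietetics) and states that "the AUD $280 cost rate will be assigned to these for service provided to patients between study entry and study exit". It adds the subscription: "Besides the AUD $85 per patient subscription there is no separate license fee for OHP". Of telephone service it says: "which is a cost to the hospital, patients are not billed and hence this cost will not be included". Strengths and Limitations describes the scope this way: "Costs are only considered from a provider perspective and limited to billable consultations".

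Telemedicine (Intervention) makes portal work a standing clinician task: "At the minimum, data are reviewed every 1 to 2 days during the week". The same section has clinicians send changes to treatment through the portal's messaging service, and it expects women to need fewer appointments as a result.

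**The concern.** The intervention moves part of the clinicians' work from the clinic to the portal. In the control arm, paper diaries are reviewed at the clinic visit (Usual Care), so that work sits inside the AUD 280 consultation. In the intervention arm, the extra reviews and messages between visits sit nowhere. A visit avoided is credited at a full fee, which the article describes as break-even and inclusive of overheads, while the portal contact that may have replaced it is priced at zero and not counted.

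The telephone rule is a separate inconsistency. Whether the patient is billed matters from a payer's point of view. The stated perspective is the provider's, and the article itself calls telephone service a hospital cost.

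At stake are two hypotheses in the Introduction: lower health service utilization and an associated provider cost saving. Both could appear confirmed while total clinician contact per woman is unchanged or higher.

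**Working it through.** The article states no cost result, so there is no figure to reproduce. The check has two parts.

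**1. What is counted and what is costed**

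| Contact | Arm | In utilization? | In cost? |
|---|---|---|---|
| Face-to-face consultation | both | yes | yes, AUD 280 |
| Telephone consultation | both | yes, as a number | no |
| Clinician review of OHP data | intervention only | no | no |
| OHP treatment message | intervention only | no | no |
| OHP subscription | intervention only | not a contact | yes, AUD 85 |

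The two rows absent from both columns belong to the intervention arm alone. Their cost cannot be negative, so leaving them out can only favour telemedicine. The telephone row belongs to both arms, so its effect depends on which arm calls more.

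**2. Illustrative size per woman**

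Inputs from the article:
- AUD 280 per consultation and AUD 85 per subscription (Data and Outcomes).
- Clinic visits of 6.22 versus 4.25 in a cited GDM study (Introduction): 6.22 − 4.25 = 1.97 visits saved.
- Reviews every one to two days over a five-day week: 5/2 = 2.5 to 5/1 = 5 per week.

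Assumptions not in the article: 4 to 12 weeks of follow-up, 3 to 15 minutes per review, AUD 50 to 100 per staff hour, and one visit equal to one billed consultation.

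Net saving by the plan's rules = visits saved × 280 − 85:
- 1.97 × 280 − 85 = 551.6 − 85 = AUD 466.6.
- The subscription is recovered at 85/280 = 0.30 visits.

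Omitted review cost = weeks × reviews per week × minutes/60 × hourly rate:
- Lowest: 4 × 2.5 × 3/60 = 0.5 h; at AUD 50, AUD 25; net 466.6 − 25 = a saving of about AUD 442.
- Middle: 8 × 5 × 5/60 = 3.33 h; at AUD 50 to 100, AUD 167 to 333; net a saving of AUD 300 to 133.
- Highest: 12 × 5 × 15/60 = 15 h; at AUD 100, AUD 1500; net 466.6 − 1500 = a loss of about AUD 1033.

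Break-even staff time is 466.6/50 = 9.3 h or 466.6/100 = 4.7 h. Over 40 reviews (8 weeks × 5) that is about 14 or 7 minutes per review.

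If only one visit were saved, the plan's figure would be 280 − 85 = AUD 195, and break-even would fall to 195/50 = 3.9 h or 195/100 = 1.95 h.

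Message time and telephone time are not in these figures.

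**The case against.** The strongest reply is that the scope is declared. The Introduction ties the cost question to savings from changes in clinic attendance. Strengths and Limitations concedes the billable-only restriction and leaves a full economic evaluation to later work. Cost is a secondary outcome of an exploratory trial. This stands as far as it goes: a cost figure that follows attendance is what the authors set out to produce. But the disclosure does not say which arm the restriction favours, and it does not touch the gap in the primary utilization outcome. The hypothesis is also worded as lower health service utilization, not merely fewer attendances.

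A second reply is that OHP activity is not wholly unmeasured, since Table 1 includes access by patients and clinicians. That is true, but it is filed under technology usage and does not enter the comparison of contacts between arms. Table 1 also mentions staff costs in its cost row, but the named source is billing data, and the article describes no charge for OHP reviews or messages.

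Several stronger readings are tempting and are not supported:
- That utilization ignores telephone contact. It does not: the number of calls is a primary indicator, so a shift from visits to calls would show there.
- That omitting telephone cost also favours telemedicine. Usual-care women may call the educators too. If OHP messages replace calls, the omission works against telemedicine.
- That the "individual semistructured 30 to 45 minutes induction" is a further hidden substitute for visits. It is a one-off session given by the lead researcher or research assistants, who have no part in routine care. What the article calls negligible is its equipment and infrastructure; staff time is not mentioned.

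**Conclusion.** The point holds for two items. Clinician OHP reviews and messages are absent from both utilization and cost, and that omission favours telemedicine. Telephone service is absent from cost on a ground that contradicts the provider perspective, with unknown direction; it could add to the first omission or partly offset it.

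A reader might infer that the expected saving is spurious. The article does not support that. The AUD 467 borrows a visit difference from another study and treats each visit as one consultation. The range from a saving of AUD 442 to a loss of AUD 1033 rests on follow-up, minutes and staff rates that the article does not give, and the middle case still leaves a saving. What can be said is that the size, and possibly the sign, of the saving depends on an input the plan does not cost. The change should be made, but the issue does not invalidate the trial.

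**What to change.** 1. Report clinician contacts by arm in separate columns: scheduled and unscheduled face-to-face, telephone, and OHP (clinician messages and review log-ins). Telemedicine (Intervention) says the lead researcher already extracts all OHP data and also messages participants for research purposes, so those messages and log-ins must be separated from clinicians' contacts.
2. Beside the billable-only figure, add a sensitivity analysis that costs OHP and telephone contacts at a staff unit cost over a stated range of minutes per contact, and report the break-even time.
3. Word any conclusion of lower utilization or provider cost saving as applying to face-to-face or billable consultations, unless it also holds under the fuller count and costing.
4. State in the limitations that leaving out OHP staff time favours the intervention arm.

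The cost is extra tabulation, largely of data already being collected, plus a unit-cost assumption. The log extract must identify clinician activity by patient, which the article does not confirm. The downside is a less favourable saving that depends on an assumed time per contact.

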**Primary**					
	Patient service utilization	Patient control	Number of scheduled face-to-face consultations	Attendances and nonattendances from outpatient activity dataset; patient medical records	Study exit
			Number of unscheduled face-to-face consultations		
			Number of telephone consultations		
**Secondary**					
	Clinical measures and satisfaction	Clinician quality of care	Glycemic control	BGL^a^ extraction from OHP^b^; glucometer downloads; patient paper diaries	Enrollment; delivery
			Glycemic stability	Time (days) to BGL stabilization	Between enrollment and delivery
			Insulin adjustments	Time (days) between insulin adjustment	Between enrollment and delivery
			Macrosomia	Fetal ultrasound biometry	2nd (17-22 weeks) and 3rd (>22 wks) trimester
			Diabetes self-efficacy	DES-SF^c^	Baseline; ≥6 weeks
			LGA^d^	Birth weight > 90th percentile	Delivery
			Neonate admission to SCN^e^	Patient medical record	Delivery
			Type of delivery (NVD^f^, LUSCS^g^, other)	Patient medical records	Delivery
			Mother/patient satisfaction with clinical care	CSQ-8^h^	Baseline; ≥6 weeks
					Enrollment; delivery
	Costs	Organization sustainability	Service provider costs	Routine billing administrative data for face-to-face/staff costs; OHP subscriptions	Study exit

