### Population, Setting, and Inclusion Criteria

The first group of participants comprises pregnant women diagnosed with GDM who have commenced insulin therapy to control hyperglycemia. These women attended outpatient GDM clinics at two tertiary hospitals between August 30, 2014, and October 30, 2016, inclusive of follow-up. One hospital is in an outer metropolitan region with a catchment population of significant cultural and linguistic diversity. The other is regionally located and serves a population with a rural background. Combined, the two hospitals have approximately 5000 live singleton births annually, and approximately 800 of the pregnancies are affected by GDM.

Women with GDM (patient participant group) are eligible for inclusion if they have a clinical diagnosis of GDM based on the IADPSG criteria following an oral glucose tolerance test [1]. Other eligibility criteria include gestation up to 35 weeks and access to the Internet via a personal computer, smartphone, or tablet. Prepregnancy glucose intolerance, twin pregnancies, GDM not treated with insulin, and other types of diabetes are exclusion factors.

The second group of participants are Credentialed Diabetes Educator Registered Nurses (CDE-RNs) who provide GDM care at the two centers. The CDE-RNs are directly involved in the RCT component of the study and provide care to women with GDM in the course of their usual practice. The number of these clinicians across the two sites is 8; all are requested to complete the clinician assessments for the study.

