### Usual Care (Control)

Usual care refers to clinical GDM care processes currently in practice at the participating hospitals, and this will be the control group. In line with recommended best practice [29,30] diagnostic screening for GDM occurs at 24 to 28 weeks gestation for women with no known history of diabetes or earlier for those considered high risk for GDM. Following diagnosis through to end of pregnancy, ongoing care is provided via a multidisciplinary team of endocrinologists, dietitians, and CDE-RNs. The role of the team is in addition to obstetric care.

From an endocrinology perspective, care involves an initial group counseling and education with a CDE-RN and dietitian covering aspects of GDM self-management. The CDE-RNs provide the pregnant women with free BGL meters from an approved supplier. The meters are individual use and the women purchase their own consumables (ie, test strips and lancing devices). Treatment targets are ≤5.0 mmol/L for preprandial BGL and ≤6.7 mmol/L for 2-hour postprandial BGLs. Insulin is initiated or titrated if BGLs are above target over three successive days. Ongoing face-to-face appointments are scheduled with members of the team as needed until delivery. Appointments generally occur every one to two weeks as determined by the clinicians. Patients on insulin have more frequent reviews especially in the early stages of insulin initiation. Self-management involves keeping a daily paper diary record of GDM self-monitoring data (1 preprandial and 3 postprandial BGLs, insulin dosing, symptoms, and dietary information). The diaries are reviewed by the clinicians at each outpatient clinic. The women also have the option to call the CDE-RNs out of scheduled appointments if BGLs are outside target.

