### Data Preparation and Analysis

Quantitative data analysis will be performed using Stata/IC 13.1 (StataCorp LP) with an intention to treat analysis. Missing data for the primary outcome is expected to be minimal as all patient appointments and outcomes are recorded. For the DES and CSQ-8 losses to follow-up will employ last observation carried forward for missing values. Since case BGL data is serial and expected to be nonlinear, case mean of nearby data points imputation will be used for missing data.

Summary univariate statistics will be used to describe the study populations and compare study groups at baseline. Categorical variables will be summarized as raw numbers and percentages and between groups comparisons will utilize chi-square statistics. Multivariate statistical analysis will be performed to compare the groups on primary and secondary outcomes. In addition, survival analysis will be performed to explore time to reach glycemic stability. Statistics will be reported with standard deviations or 95% confidence intervals as appropriate. Statistical significance will be indicated by *P*<.05.

Patient and clinician interviews will undergo thematic analysis supported by NVivo 11 (QSR International). The interview transcripts will be analyzed separately for each participant group using an inductive approach to identify and/or infer themes and codes from the transcripts. Further themes will be classified according to the dimensions of telehealth evaluation framework [41].

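### Days between insulin adjustments cannot be computed for every randomized woman and can understate a difference between the arms, by an amount that depends on how often insulin is adjusted

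*Protocol article*

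**What the plan says.** Table 1 lists insulin adjustments among the secondary clinical measures. It defines them as "Time (days) between insulin adjustment", with the time point "Between enrollment and delivery". It does not say where the first interval starts, how several intervals in one woman are summarized, or what value a woman with no adjustment or only one receives.

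Other sections set the conditions under which adjustments occur:
- Population, Setting, and Inclusion Criteria: participants are "pregnant women diagnosed with GDM who have commenced insulin therapy to control hyperglycemia", so the start of insulin normally precedes entry. Entry can be late: "Other eligibility criteria include gestation up to 35 weeks".
- Usual Care (Control): "Insulin is initiated or titrated if BGLs are above target over three successive days". On review frequency: "Appointments generally occur every one to two weeks as determined by the clinicians", with more frequent review for women on insulin.
- Telemedicine (Intervention): "At the minimum, data are reviewed every 1 to 2 days during the week". Feedback through the portal may include changes to insulin.

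Data Preparation and Analysis says that the quantitative analysis will be done "with an intention to treat analysis". Secondary outcomes are to be compared by an unspecified multivariate analysis. Survival analysis is named for time to glycemic stability only. The missing-data rules cover the two questionnaires and the glucose series, and the section expects little missing data for the primary outcome.

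**The concern.** A gap between adjustments needs two adjustments. If the first gap may run from enrollment or from the start of insulin, it needs one. Women below that number have no value. No imputation rule in the article can supply one, because nothing went unrecorded: the quantity does not exist for them.

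The number of adjustments arises after randomization. Telemedicine data are looked at far more often than a clinic diary is, so the intervention may well change that number. Women with a computable gap are then a selected group, and the selection can differ between arms.

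Delivery adds a second problem. A long interval is less likely than a short one to be completed before follow-up ends. If only completed gaps are used, the arm with rarer adjustments loses more women and also more of its long gaps. Both effects pull the arms together. What is at stake is whether a real difference in titration frequency would be seen, and whether the comparison is still between the randomized groups.

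**Working it through.** The article gives no figure for this outcome, so there is none to reproduce. Its stated sample size of 42 concerns clinic visits and has no bearing here.

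**Inputs.** From the article: 100 women, 1:1 (50 per arm), significance at P<.05 (two-sided assumed), window from enrollment to delivery, entry up to 35 weeks. Assumed: adjustments follow a Poisson process at rate r per week; time on study T is uniform from a = 3 to b = 14 weeks. If delivery is near 39 weeks, entry at 35 weeks leaves about 4.

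**Step 1: women without a value.** For a given T, P(fewer than two) = e^(−rT)(1 + rT). Averaged over T:

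share = [(2 + ra)e^(−ra) − (2 + rb)e^(−rb)] / [r(b − a)]

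- r = 0.25: (2.75 × 0.4724 − 5.5 × 0.0302) / 2.75 = 0.41
- r = 0.5: (3.5 × 0.2231 − 9 × 0.0009) / 5.5 = 0.14
- r = 1.0: (5 × 0.0498 − about 0) / 11 = 0.02

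If one adjustment is enough, the share lost is [e^(−ra) − e^(−rb)] / [r(b − a)]. This gives (0.4724 − 0.0302)/2.75 = 16% at 0.25 per week and (0.2231 − 0.0009)/5.5 = 4% at 0.5.

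**Step 2: unequal loss.** For 0.35 per week the first formula gives (3.05 × 0.3499 − 6.9 × 0.0074)/3.85 = 0.26. With 0.35 in one arm and 0.5 in the other, 50 × 0.26 + 50 × 0.14 = 13 + 7 = about 20 of 100 women have no value, nearly twice as many in one arm as in the other.

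**Step 3: attenuation.** In simulated trials of 50 per arm with a true gap ratio of 0.50 and no variation in rate between women, using completed gaps only:

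| Window | Rates per week | Women with a value | Observed ratio | Power, mean gap (t-test) | Power, rate in all women |
|---|---|---|---|---|---|
| 4 weeks | 0.25 v 0.5 | 27% v 59% | 0.90 | 0.06 | 0.99 |
| 3.5–12 weeks | 0.25 v 0.5 | 55% v 85% | 0.73 | 0.42 | 1.00 |
| 3.5–12 weeks | 0.5 v 1 | 85% v 98% | 0.59 | 0.98 | 1.00 |
| 3.5–12 weeks | 1 v 2 | 98% v 100% | 0.52 | 1.00 | 1.00 |

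The first row is the late-entry case. With 3.5–12 weeks and 0.25 v 0.5 per week, true gaps of 28 and 14 days appear as 15.6 and 11.3.

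**Step 4: smaller effects and overdispersion.** With 3–14 weeks on study and 0.35 v 0.5 per week, power is about 27% for the mean gap and 91% for the rate. If rates vary between women (gamma frailty, variance 0.5), these fall to about 13% and 51%. At 1 v 1.5 per week without frailty, about 1 woman in 100 is excluded and the mean gap has 98% power. With frailty, in the 3.5–12 week window, the same rates give 29% for the mean gap (t-test) and 71% for the rate.

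**The case against.** The strongest reply is that the article fixes only a measure and a window. It does not prescribe a mean of completed gaps, exclusion of women with few adjustments, or a t-test. The same intervals, measured from enrollment and censored at delivery, would keep everyone. Under a constant rate, the likelihood for a woman with N adjustments in time T is then proportional to r^N e^(−rT), which is the Poisson model with log time as offset. The rate-analysis power is therefore equally available to an interval measure analysed that way, and such an analysis could stand in a plan that is not shown. This stands as far as it goes. But the article names a censoring method for one outcome and not for this one, and the measure as worded does not lead a reader to a censored analysis.

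Three stronger readings are tempting, and the documents do not support them:
- A reader might infer that the measure contradicts intention to treat. No sentence excludes any woman. What can be said is that the measure, as worded, cannot be computed for all randomized women.
- A reader might infer that a value always requires two adjustments. The start of the first interval is not stated, so one might suffice.
- A reader might infer that the measure largely hides a real difference. That depends on rates that the article does not give. It describes active titration and frequent review, and at about one adjustment per week without frailty the loss is small.

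It is also fair that an interval expresses timely response, which is the premise of the intervention, more directly than a rate does.

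**Conclusion.** The point holds in a limited form. As worded, the measure has no value for women with too few adjustments, drops the interval open at delivery, and so selects on a post-randomization count that the intervention can change. In every simulated scenario with few expected adjustments the observed difference was closer to none than the true one, and the rate analysis was at least as powerful throughout.

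The size is uncertain. It is severe when control women average about two or fewer adjustments, or when follow-up is only a few weeks, and negligible at about one adjustment per week over longer follow-up without frailty. Variation between women makes the gap measure weaker at all rates examined, but it also lowers the power of the rate analysis, so the 91% is an upper figure. All of this rests on assumed Poisson rates, assumed time on study and an analysis of completed gaps. The outcome is secondary in an exploratory trial, so this deserves correction without threatening the trial's main conclusion.

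**What to change.** In Table 1, define the outcome as the number of insulin adjustments per woman from enrollment to delivery. In Data Preparation and Analysis, state that it is analysed in all randomized women with a negative binomial or robust Poisson model, with log time from enrollment to delivery as offset. A woman with no adjustments then contributes a zero.

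If a timing measure is kept, analyse gap times starting at enrollment as recurrent events censored at delivery, and say so.

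The cost is one table line and one sentence of analysis. Insulin dosing is part of the self-monitoring record that is already extracted from the portal or copied from paper diaries. Table 1 names no separate source for this row, so it should be confirmed that adjustments can be identified equally well in both arms. The price in interpretation is small: a rate describes timeliness less directly than an interval does.
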